### 4.3. Randomization:

An age-stratified approach to treatment group assignment using two age groups (6-59 months and 5 years and above) will be used. Randomisation lists shall be generated in the Kampala office by a member of the project who will not be directly involved in the conduct of the study. Two separate allocation schedules (A and B) shall be generated. A sealed copy of the original randomisation lists and documentation of the procedure used to generate the lists will be stored in the project administrative offices in Kampala. Prior to the onset of the study, sealed copies of the randomization lists will be distributed to the study nurse responsible for treatment allocation.

### 4.4. Treatment allocation and masking:

On the day of enrolment, study participants will undergo baseline evaluations and be assigned a study number by the clinicians. Patients will then be referred to the study nurse who will be responsible for the treatment group assignment and allocation of the study medications. The study nurse will note the patient’s age and select the next available treatment number and corresponding assigned treatment. The study nurse will record directly onto the randomization list the date and time of treatment assignment and study number. Once a month, a copy of the updated randomization list will be placed by the study nurse into sealed envelopes and delivered to the administrative office in Kampala where they will be stored securely. The original randomization list will be crosschecked to assure adherence to the randomisation code. Initial studies will involve one of the two following treatment comparison designs:

1. Two-arm study – CQ/SP vs. AQ/SP
2. Three-arm study - CQ/SP vs. AQ/SP vs. AQ/AS

Sentinel sites with previously identified low levels of drug resistance and/or lower-level capacity for the conduct of complex studies will be chosen for the two-arm study. Sentinel sites with previously identified higher levels of drug resistance and greater capacity will be chosen for the three-arm study.

The nurse shall administer study medications according to weight-based guidelines (Appendix 4). Study medications will not be identical in appearance or taste, however other procedures will be followed in an attempt to mask the patients to their treatment. Patients will not be informed of their treatment regimen and identical dosing regimens will be used in all the treatment arms. In studies where AS/AQ shall be compared with CQ/SP and AQ/SP, patients assigned to CQ/SP and AQ/SP shall be given a placebo (lactose tablets) on day 1 and day 2 in the same amount as AS. Administration of study medications will be directly observed. Any patient who vomits the medication within 30 minutes of administration of the drugs will be retreated with a second dose. If the patient vomits repeatedly on Day 0, they shall be excluded. If the patient vomits repeatedly on Day 1 or 2 and is unable to retain the dose of the study medication, the patient will be classified as a treatment failure and referred for appropriate care with parental antimalarial medication.

All members of the study group who will be involved in assessment of patient outcomes following treatment for uncomplicated malaria including the study physicians (responsible for clinical assessment and measurement of temperature) and laboratory technicians (responsible for reading thick blood smears and determining parasite density) will be blinded to the treatment group assignments.

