### 6.2. Treatment group assignment:

At the time of enrolment, patients will be randomly assigned to one of the treatment groups. Randomisation shall be according to a pre-determined randomisation list stratified by age. Treatment allocation and administration of medications will be done by the study nurse who will not be involved in outcome classification and will remain the only member of the study team not blinded to the treatment groups.

Administration of study medications will be performed by the study nurse and will be directly observed (Appendix 4). Any patient who vomits the medication within 30 minutes of administration of the drugs will be retreated with a second dose. If the patient vomits repeatedly on Day 0, and is unable to retain the dose of the study medication, the patient will be excluded from the study.If this occurs on Days 1 or 2, the patient will be classified as a treatment failure, referred for appropriate care and treated with parenteral antimalarial medication.

Patients will receive acetaminophen 10 mg/kg with instructions to take it every 8 hours until the resolution of fever. Any child with a hemoglobin of < 10.0 gm/dl will be treated with iron sulfate for 2 weeks and mebendazole (only those aged 1 - 5 years).

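### Once the site randomisation list is in use, the allocating nurse can see upcoming assignments, and no per-patient concealment is described

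*Protocol*

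**What the plan says.** Section 4.3 covers how the sequence is made and delivered. Generation is independent of the sites: a project member with no direct part in running the trial makes the lists in Kampala. There are two schedules, A and B, and two age strata (6-59 months; 5 years and above). A sealed copy of the originals stays in the Kampala office. Before the study starts, "sealed copies of the randomization lists will be distributed to the study nurse responsible for treatment allocation".

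Section 4.4 covers use at the clinic. First, "study participants will undergo baseline evaluations and be assigned a study number by the clinicians". The patient is then referred to the nurse, who notes the age and must "select the next available treatment number and corresponding assigned treatment". The entry is made on the list itself: "The study nurse will record directly onto the randomization list the date and time of treatment assignment and study number". Each month the nurse sends Kampala, in a sealed envelope, a copy of the list as filled in so far, and "The original randomization list will be crosschecked to assure adherence to the randomisation code".

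Section 6.2 adds that the nurse who allocates also gives the drugs, takes no part in outcome classification, and "will remain the only member of the study team not blinded to the treatment groups". Section 4.4 blinds the study physicians and laboratory technicians who assess outcomes.

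The protocol mentions no individual envelope, coded pack, covered list line or central call.

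**The concern.** Concealment means that nobody who can influence which patient takes the next place knows what that place holds. Here the seal is on the list as delivered. From the first allocation, the person who assigns treatment has the remaining sequence in view.

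That opens three routes: taking a line out of order, influencing which eligible patient comes next, or letting enrolling staff know what is coming. Any of these could make the arms differ in prognosis before treatment. Section 8.2 plans an age-stratified analysis and logistic regression for imbalance in potential confounders. Those methods deal with measured factors. They would not remove differences in unmeasured factors, nor differences in age within a stratum unless age were also put in the model. The primary comparison of clinical failure at 28 days would then carry a bias whose size could not be known afterwards.

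**Working it through.** The point is settled by reading the procedure in order, not by a calculation.

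1. *Is the list sealed in use?* Section 4.3 seals the lists for distribution. Section 4.4 then has the nurse read a treatment from the list and write on it for each patient. Both cannot hold after the first patient unless single lines are covered, and nothing says they are. So the nurse can see later lines, on the list for each age stratum.
2. *Who decides entry?* Clinicians conduct the screening interview and obtain consent (section 5.3) and give the study number before referral (section 4.4). They are blinded and do not hold the list. For them concealment fails only if the nurse discloses.
3. *What can the cross-check show?* The natural reading is that the used list is compared with the original held in Kampala. Appendix 1 passes an excluded patient's study number to the next subject, which suggests that study numbers run in order. A treatment line taken out of turn could then show as a mismatch between study-number order and treatment-number order within a stratum. A patient sent forward earlier or later, or a disclosed assignment, leaves no such trace. The check also comes up to a month after the event.

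**The plan's own figures, for context only.** The sample sizes in section 8.1 reproduce with the two-proportion formula, two-sided α 0.05, power 80%, with continuity correction. For 15% vs 5%:

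- n = [1.960·√(2·0.10·0.90) + 0.842·√(0.15·0.85 + 0.05·0.95)]² / 0.10² = 140.1
- corrected: (140.1/4)·[1 + √(1 + 4/(140.1·0.10))]² = 159.5, so 160, as stated

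For 10% vs 2% the same formula gives the stated 162. Allowing for 10% loss, 160/0.9 gives 178 and 162/0.9 = 180; the protocol uses 180 for both. At 180 per group the lists hold 2 × 180 = 360 lines for a two-arm study and 3 × 180 = 540 for a three-arm study. These are totals at the start, split over two age strata and shrinking with each patient.

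**Illustration on assumed values.** Take 160 per arm, no true treatment difference, an overall failure risk p of 10% or 15% (assumed), and steering that moves the arms' underlying risks apart by d. With s0 = √(2p(1−p)/160), s1 = √{[a(1−a) + b(1−b)]/160}, a = p + d/2 and b = p − d/2, the two-sided 5% test rejects with probability 1 − Φ[(1.96·s0 − d)/s1] + Φ[(−1.96·s0 − d)/s1]. For p = 10% and d = 2 points, s0 = 0.03354 and s1 = 0.03352, which gives 0.086 + 0.005 = 0.091.

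| d (points) | p = 10% | p = 15% |
|---|---|---|
| 0 | 5.0% | 5.0% |
| 1 | 6.0% | 5.7% |
| 2 | 9.1% | 7.9% |
| 3 | 14.5% | 11.7% |
| 5 | 31.9% | 24.0% |

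The protocol does not say which row, if any, would apply.

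**The case against.** The strongest reply is that roles are separated. Eligibility, consent and numbering are finished by blinded clinicians before the nurse acts, outcome assessors are blinded, each assignment is dated and timed, and Kampala holds an independent original. All of that stands. It reduces the risk and makes some departures traceable, but no physical barrier stands between the nurse and the next line.

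The reply also rules out several stronger readings that a reader might infer:

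- *That allocation is not concealed at all.* The people who decide entry never hold the list. Concealment from them depends on one person's discretion, which is weaker than it should be but not absent.
- *That the cross-check is empty.* It uses an original held elsewhere and may show out-of-sequence use.
- *That the choice of age list is a free hand for the nurse.* The stratum follows from age, which is recorded on the screening and case record forms, so a wrong list could be traced.
- *That the Day 0 vomiting rule is part of the same fault.* After repeated vomiting on Day 0, "the patient will be excluded from the study". This happens after assignment and dosing, when the nurse knows the arm under any concealment method. Envelopes would not change it.
- *That a large bias can be read off.* Placing nine certain failures in an arm of 180 would add 9/180 = 5% × (1 − 0.15 to 1 − 0.05), about 4.3 to 4.8 points, against a planned difference of 10. That assumes all nine are recognised in advance and all go to one arm. Nothing in the protocol supports it.
- *That no analysis could help.* Stratification by age and adjustment for measured factors would remove part of an imbalance.

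**Conclusion.** The point holds as a design risk. Sections 4.3 and 4.4, as written, leave upcoming assignments visible to the person who allocates, with partial safeguards that act through that person's discretion or after the event. The conclusion rests on one inference: a list read from and written on for every patient is open while in use, and the protocol describes no covering of single lines.

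The documents contain no steering rate, so the size is unknown. The table shows only that a gap of 2 to 3 points in underlying risk would raise the false-positive rate from 5% to about 8-15% under the stated assumptions. Nothing in the protocol is evidence that steering occurred, and a reader should not infer it. The reason to act is that the remedy is cheap and must be in place before enrolment.

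**What to change.** Replace the list at the clinic with sequentially numbered, opaque, sealed envelopes, or pre-numbered coded packs, with one series per age stratum. The nurse opens the next one only after writing the patient's study number, age, date and time on the outside. The full list stays in Kampala only. Amend sections 4.3, 4.4 and 6.2 to match, and direct the monthly check at the used envelopes or packs, comparing their order with the order of study numbers in each stratum.

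The cost is preparing envelopes or packs before each site starts. Staff, sample size and treatment do not change. The nurse will still know each arm once it is opened, so this protects the sequence ahead and not the masking of the person who gives the drugs.

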### 5.0 PARTICIPANT SELECTION AND ENROLLMENT.

### 5.1. Recruitment and screening process:

Study subjects will be recruited from the OPD (outpatient department) of sentinel health centres. Patients who present with symptoms suggestive of malaria (fever or history of recent fever) will be referred to the outpatient laboratory/study laboratory for a screening thick blood smear (using standard Giemsa staining). Thick blood slides will be read and counted by the outpatient/study laboratory technicians. The parasite density of positive screening thick blood smears will be estimated by the outpatient laboratory technicians by counting the number of asexual parasites per 200 leukocytes, assuming a leukocyte count of 8,000/l. All patients who have a positive screening thick smear with a parasite density of > 2000/ul (>13 parasites per 200 leucocytes) and < 200,000/ul will be referred for further evaluation. After referral to the study clinic, the screening interview will take place. If the patient satisfies the selection criteria, they will be enrolled in the study. All patients who do not satisfy the selection criteria and are excluded from study enrolment will be referred back to the outpatient department for appropriate care.

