### 5.2. Selection criteria:

Patients shall be assessed for the inclusion criteria at the time they are referred to the study clinic with a screening thick blood smear parasitaemia of > 2000/ul and < 200,000/ul. If the following criteria are met, patients will be enrolled in the study, assigned a study number, have blood removed by finger-prick for further laboratory tests (Giemsa-stained thick and thin blood smears, Hb measurement and blood collected on filter paper) and will be treated promptly according to their assigned antimalarial study regimen.

1. Age 6 months and above.
2. Fever (> 37.5ºC axillary) or history of fever in the previous 24 hours.
3. Absence of any history of serious side effects to study medications, including allergy to sulphonamide drugs
4. No evidence of a concomitant febrile illness which could interfere with the assessment of clinical treatment outcome
5. Provision of informed consent and ability to participate in 28-day follow-up (patient has easy access to health unit).
6. No history of treatment with an antifolate (sulfadoxine-pyrimethamine [single dose], metakelfin [single dose], TMP/Sulfa [> 3 days]) or amodiaquine (> 2 doses) during the last week (taking final dose within the 7 days prior to study enrolment).
7. Absence of pregnancy (menstruating women who have not missed their last menstrual period).
8. No danger signs or evidence of severe malaria defined as:

- Unarousable coma (if after convulsion, > 30 min)
- Repeated convulsions (> 2 within 24 h)
- Recent convulsions (1-2 within 24 h)
- Altered consciousness (confusion, delirium, psychosis, coma)
- Lethargy
- Unable to drink or breast feed
- Vomiting everything
- Unable to stand/sit due to weakness
- Severe anemia (Hb < 5.0 g/dL)
- Respiratory distress (laboured breathing at rest)
- Jaundice (yellow coloring of eyes)

Prior to the Day 1 return visit, the study laboratory technicians shall assess the results of the Giemsa-stained thick and thin blood smears. These shall not be available until after the patients have been treated and discharged from the clinic. Additional patients will be excluded from the study on Day 1 if they fail to meet the following additional inclusion criteria.

1. *P. falciparum* mono-infection
2. Parasite density > 2000/ul and < 200,000/ul.

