Any patient who is excluded on Day 1 will be treated and followed-up in a clinically appropriate manner, but will not be followed for the 28-day period. The study number and treatment number of a patient excluded on Day 1 will not be re-assigned.

5.3. Process for obtaining informed consent:

Study clinicians shall conduct the screening interview and seek formal consent in the clinic. Once it has been determined that the subject meets the study entry criteria during the screening interview, all study details will be carefully discussed with the subject or their parents/guardian. All interviews shall be conducted in the native language of the patients and parents/guardians of children. Consent forms will be available in both English and the local language. Following the informed consent discussion, the patient or parents /guardians of children shall be asked to sign a written consent form. If they are unable to read and write, a fingerprint will be used in substitute for a signature and a witness will be asked to sign the form to document that the informed consent process was adequately conducted.

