### 6.0 BASELINE EVALUATION AND TREATMENT ASSIGNMENT

### 6.1. Baseline evaluation and procedures:

On Day 0, patients enrolled and assigned study numbers will undergo a complete history and physical examination (Appendix 5 and 6). On day 0, a finger-prick blood sample will be obtained for repeat thick blood smear, thin blood smear, haemoglobin measurement and to save on filter paper for future molecular testing. Because only rapid Giemsa-stained thick smears are typically assessed in the outpatient laboratory, a thick and thin blood smear obtained at enrolment will be stained with 2% Giemsa and read by experienced laboratory technicians who are not involved in direct patient care. Parasite densities will be calculated by counting the number of asexual parasites per 200 leukocytes (or per 500, if the count is <10 parasites/200 leukocytes), assuming a leukocyte count of 8,000/l. A blood smear will be considered negative when the examination of 100 high power fields does not reveal asexual parasites. Gametocytemia will also be determined from thick smears. Thin smears will be used for parasite species identification.

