### 8.0 STATISTICAL CONSIDERATIONS

### 8.1. Sample size calculations:

The sample size calculations will be made for each study based on the estimated efficacy of the combination regimens to be studied in the given region. For the purposes of sample size calculation, the risk of clinical failure at 28 days will be the main outcome. If the null hypothesis states that there is no difference in clinical outcome between the treatment groups, we plan to test the alternative hypothesis that treatment with an alternative combination regimen (AQ/SP or AS/AQ) will decrease the likelihood of clinical failure at 28 days of follow-up. Calculations will be made using an α = 0.05 and a statistical power of 80% based on a two-sided test. Allowance will be made for a possible 10% loss to follow-up to ensure that an adequate number of patients complete the study. Based on this, the sample size for the various drug combinations is summarized below:

Sample size for the different drug combinations

| **Presumed level of resistance.** | Resistance to CQ/SP | Resistance to AQ/SP or AS/AQ | Number per group | Number per group adjusted for loss to follow up. |
| --- | --- | --- | --- | --- |
| High resistance community (urban areas) | 15% | 5% | 160 | 180 |
| Low resistance community (rural areas) | 10% | 2% | 162 | 180 |

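### The screening count printed in Protocol 5.1 as the equivalent of 2000/ul (>13 parasites per 200 leucocytes) is 520/ul by the protocol's own method; 2000/ul is 50 per 200.

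*Protocol*

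**What the plan says.** Section 5.1 sets the referral rule at the outpatient bench. Density is estimated by "counting the number of asexual parasites per 200 leukocytes, assuming a leukocyte count of 8,000" per microlitre (the micro sign in the unit appears to have been lost in text extraction). The next sentence refers patients with a "positive screening thick smear with a parasite density of > 2000/ul (>13 parasites per 200 leucocytes"), subject also to an upper limit of 200,000/ul.

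The enrolment smear in section 6.1 uses the same conversion, with a larger denominator only for low counts: "or per 500, if the count is <10 parasites/200 leukocytes), assuming a leukocyte count of 8,000".

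Elsewhere the lower limit appears as a density alone. Section 5.2 speaks of patients "referred to the study clinic with a screening thick blood smear parasitaemia of > 2000/ul and < 200,000/ul", and the Summary, section 7.1, Appendix 1 and the screening form in Appendix 8 also give 2000/ul without a count. The figure of 13 occurs once, in section 5.1.

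The sequence after referral also matters:
- Randomisation and the first observed dose take place on Day 0 (sections 4.4 and 6.2).
- The definitive Giemsa result becomes available only after the patient has been treated and sent home (section 5.2).
- Patients outside 2000 to 200,000/ul on that smear are excluded on Day 1 and are not followed for 28 days.
- On numbering, section 5.2 says "The study number and treatment number of a patient excluded on Day 1 will not be re-assigned".

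**The concern.** One sentence gives two lower limits for the same decision, and under the protocol's own conversion they differ nearly fourfold. The bracketed figure is the only raw count the protocol gives for the lower limit, and a raw count is what a reader at the microscope can apply directly.

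The error acts at a point where it cannot be undone. Between referral and the first dose there is no second density reading, so a patient admitted on the wrong count is found only after randomisation and treatment. At stake are exposure of patients who do not meet the entry criterion, and allocations spent on patients who will not be followed or analysed.

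**Working it through.** **Inputs.** Leukocytes counted: 200 (5.1). Assumed leukocyte count: 8,000/ul (5.1 and 6.1). Lower density limit: 2000/ul (5.1, 5.2 and elsewhere). Printed equivalent: more than 13 per 200 (5.1).

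**Conversion.** Density = parasites counted x (assumed leukocytes per ul / leukocytes counted) = count x 8000/200 = count x 40.

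**Trying to reproduce the plan's figure.**
- The printed count: 13 x 40 = 520/ul. That is 520/2000 = 26% of the limit, too low by a factor of 2000/520 = 3.8.
- The count that matches the limit: 2000 x 200/8000 = 50 per 200.
- The lowest count that passes the printed rule: 14 x 40 = 560/ul.
- Counts of 14 to 50 per 200, or 560 to 2000/ul, therefore pass the printed count but do not exceed the density limit.

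**Could another convention rescue 13?**
- With 200 leukocytes counted, 13 equals 2000/ul only if the assumed leukocyte count is 2000 x 200/13, about 30,800/ul. Assumed counts of 4,000 to 12,000/ul give 13 x 4000/200 = 260/ul up to 13 x 12000/200 = 780/ul.
- With 8,000/ul and 100 leukocytes counted, 13 is 1040/ul; with 500 counted, it is 208/ul.
- With 50 leukocytes counted, 13 x 8000/50 = 2080/ul, which is close. A rule of 13 per 50 printed with the wrong denominator is a plausible origin, but nothing in the protocol says so.

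**Following the consequence through.** For a patient at, say, 30 per 200 (30 x 40 = 1200/ul):
1. The printed count refers the patient; the density limit would not.
2. Section 5.2 takes the screening result as given.
3. The patient is randomised and dosed on Day 0 (6.2).
4. If the definitive smear agrees with the screening smear, the patient is excluded on Day 1 (5.2), and the treatment number is used up.

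**Power, for illustration only.** Section 8.1 states: "Allowance will be made for a possible 10% loss to follow-up". The table's 160 (15% v 5%) and 162 (10% v 2%) per group reproduce exactly with the two-sided two-proportion formula at 5% and 80% power with continuity correction; without the correction they are 141 and 138. Dividing by 0.9 gives 178 and 180, against the printed 180.

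Suppose that 180 counts patients before the Day 1 check, and that a fraction x is excluded on Day 1. Then n per group = 180 x (1 - x) x 0.9. No value of x is given, so a range is shown:

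| Assumed x | n per group | Power, corrected (15 v 5; 10 v 2) | Power, uncorrected (15 v 5; 10 v 2) |
|---|---|---|---|
| 5% | 154 | 78%; 78% | 84%; 84% |
| 10% | 146 | 76%; 75% | 82%; 82% |
| 20% | 130 | 70%; 69% | 77%; 78% |
| 30% | 113 | 63%; 62% | 71%; 72% |

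**The case against.** The arithmetic is not open to dispute, but the consequences are.

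**Density is the operative criterion.** Section 5.1 tells the technician to estimate a density, and the limit is written as one. A technician who does that screens correctly, and every other statement of the limit is a density. This stands. The error permits wrong referrals; it does not show that they will happen, or how often.

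**Day 1 exclusion is designed in.** Discordant readings and mixed infections would cause some exclusions in any case. This also stands; a wrong count would add to them.

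**Bias.** A reader might infer that exclusions after randomisation distort the comparison between arms. The protocol does not support that. The exclusion rests on a sample taken at baseline and read by technicians blinded to treatment (4.4, 6.1), and section 8.2 limits the primary population to randomised patients who meet the selection criteria. The 2000/ul limit is thus still enforced in the analysis.

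**Power.** A reader might also infer that Day 1 exclusions come straight out of the 160 or 162 per group, so that the trial is underpowered. That is not established, for four reasons:
- Section 8.1 does not say whether 180 counts patients before or after the Day 1 check.
- Not re-assigning a number stops an allocation being recycled; it does not prevent further enrolment from the list.
- Every exclusion rate in the table is an assumption.
- The answer depends on the test. Section 8.2 plans chi-square or Fisher's exact tests, and with an uncorrected chi-square power is still about 82% at an assumed 10% exclusion rate.

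**Rescuing the count.** The possible 13-per-50 origin would explain the slip, but the printed denominator is 200, so it does not make the text right.

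**Conclusion.** The point holds as an error in an eligibility figure. Under the protocol's own counting method, 13 per 200 is 520/ul and 2000/ul is 50 per 200. This needs no assumption beyond reading the leukocyte count as 8,000 per microlitre.

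The practical consequence is conditional. Where screening staff use the printed count in place of the calculated density, patients at 560 to 2000/ul can be referred, randomised and dosed, then excluded on Day 1. Nothing in the protocol catches them before the first dose. The number affected cannot be derived, because neither the distribution of screening densities nor a Day 1 exclusion rate is given.

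The harm is avoidable exposure and wasted randomisations. Neither bias between arms nor a loss of power is shown. It should be corrected before screening starts, because the figure acts ahead of an irreversible step and is simple to put right.

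**What to change.** In section 5.1, replace ">13 parasites per 200 leucocytes" with >50 parasites per 200 leucocytes. This sets no new threshold; it makes the count agree with the 2000/ul used throughout the rest of the protocol. If any screening instruction or training material repeats the 13, correct it too, and brief the screening technicians.

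The cost is one figure and a short briefing. Where the printed count would have been used, somewhat fewer patients will be referred from the bench; those no longer referred are patients who would not have met the density limit.
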